### Health economic evaluation

The health economic analysis will conform to a superiority trial analysis and will address both cost-effectiveness (cost per unit of improvement of the primary outcome – the FFIpain) and cost utility using quality-adjusted life years measured using the EQ-5D-5 L.

Costs of treatment in either arm will be considered from a societal perspective. For prefabricated FOs, the costs collected will include the unit cost of each prefabricated device prescribed, and staff time for assessments and review appointments. Similarly for customised FOs, the costs collected will include costs associated with manufacture of FOs including materials and staff time, as well as staff time for assessments and review appointments. In addition, the costs of systemic therapies in terms of biological agents, disease-modifying anti-rheumatic drugs and non-steroidal anti-inflammatories will be recorded for both trial arms.

For both trial arms and in addition to FOs related costs, we will record the use of foot care services throughout the trial. These will be costed using National Health Service pay and prices or, where appropriate, using other (e.g. shop or internet bought) sources. Out of pocket expenses for over the counter products, and complementary and alternative therapies, as well as travel to/from health appointments and time off work will also be included. All cost data will be collected using a combination of participant medical records, and an adapted version of the Client Service Receipt Inventory [58] resource use checklist. Data on programme costs and those on further impacts will be aggregated and the statistical significance of differences in cost per patient between trial arms assessed by appropriate methods depending on the distributional characteristics of the data.

### Sample size

In the absence of availability of detailed information on the clinical meaningful difference in outcome measured using the FFI pain subscale, the calculation of our desired effect size was based upon previous findings from an FOs trial for people with RA [52]. This trial evaluated 6 month FFI pain subscale scores at 6 months following intervention with either a functional FO versus a non-functional placebo-type flat FO. Mean difference at 6-month outcome (9.93) and pooled standard deviation (19.77) values were obtained from this study to calculate a standardised mean difference. For a two-tailed hypothesis, to detect a standardised mean difference of 0.5 (9.93/19.77) (a medium to large effect size) at 0.05 significance, 0.8 power and 20% attrition (based on the randomised controlled trials by Woodburn et al. [30]), we require 160 participants (80 per arm) [Statistics Calculators, 2015].

### Recruitment

Participants meeting the selection criteria will be recruited from ‘early arthritis’ rheumatology outpatients’ clinics within the National Health Service Health Boards/Trusts of the participating centres.

### Randomisation

Randomisation will be conducted via permuted block. This means there will be variable size blocks with allocation to customised (a) or prefabricated (b) for 160 participants. In order to conceal the process from local trial site personnel, this will be administered via web randomisation. Permuted block randomisation will be performed using a bespoke Fortran program with an intrinsic pseudo-random number generator and the resulting table will be accessed by a bespoke Fortran web application on a secure server, to provide and log allocations sequentially on-line as required. Each intervention podiatrist will have access to a web ‘link’ which will randomly allocate the participants into each arm. This will be undertaken by the intervention podiatrists once they have concluded their respective foot assessments.

### Allocation concealment

Allocation will be conducted once eligibility checks have been performed and only once the participant has been registered in the trial. The central randomisation administrator who will follow the web based allocation will be masked to the identity of participants and all primary and secondary outcomes.

### Blinding/masking

The nature of this trial dictates that blinding of the clinicians delivering interventions and the participants is not possible. However the outcome assessor will be blind to group allocation, and will not be involved in any delivery of therapeutic interventions. Participants will be instructed not to disclose their group allocation to the outcome assessor. Any breaches in blinding protocol will be recorded.

### Analysis

Data will be analysed according to the intention-to-treat principle. Data will be explored to determine whether or not potential confounders need to be accounted for in the final analysis. Should we detect any imbalances between intervention groups, we expect that the analysis of the primary outcome (FFI pain subscale) will be conducted using an analysis of covariance (ANCOVA) with adjustment for relevant baseline values and potential confounders. For example, to account for systemic disease activity as a covariate, the FFI pain subscale change scores will be adjusted according to both FFI pain subscale baseline scores and the change scores of the Disease Activity Scale for 28 joints between baseline and follow up. Statistical methods for secondary/additional analyses: Similarly, for comparison of all other secondary outcomes, between group scores from baseline to 12 months will be compared using ANCOVA with adjustment for baseline values and potential confounders. All estimates for primary and secondary outcomes will be reported with estimated effect sizes alongside 95% confidence intervals.

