### Study outcome measures

The primary outcome measure will be foot pain, which will be measured at 12 months using the Foot Function Index pain subscale (FFI_pain_), which is a composite score for foot pain [51]. The FFI is a widely used, valid and reliable self-administered questionnaire consisting of 23 items grouped into 3 domains: foot pain (9 items), disability (9 items), and activity limitation (5 items) [51]. At present, the FFI is one of the few instruments for scoring foot-related disability that has been rated positively for responsiveness-to-change [6] and has been employed frequently as a primary outcome measure in several previous RCTs of FOs for people with RA [16, 52, 53]. For each subscale, items are rated using a 100 mm Visual Analogue Scale, and a composite score is calculated by summing items and dividing by the total number of items in that subscale. As outlined in the original scoring system [51] any item marked as not applicable will be excluded from the calculation of the total possible score. A higher score is indicative of more severe foot pain and disability.

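### Baseline adjustment of the primary outcome hangs on an undefined finding of imbalance, so the primary model depends on the data and the precision from baseline FFI pain may be lost

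*Protocol article*

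**What the plan says.** The Analysis section sets out a sequence. First, "Data will be explored to determine whether or not potential confounders need to be accounted for in the final analysis". Then the condition: "Should we detect any imbalances between intervention groups, we expect that the analysis of the primary outcome (FFI pain subscale) will be conducted using" an ANCOVA with baseline values and potential confounders as covariates. An example follows, in which "the FFI pain subscale change scores will be adjusted according to both FFI pain subscale baseline scores and the change scores of the Disease Activity" score in 28 joints. Baseline FFI pain enters the primary analysis only inside this condition.

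For the secondary outcomes the section says that "between group scores from baseline to 12 months will be compared using ANCOVA with adjustment for baseline values and potential confounders". The imbalance condition is not repeated there.

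Study outcome measures fixes the endpoint: "The primary outcome measure will be foot pain, which will be measured at 12 months using the Foot Function Index pain subscale". Sample size rests on a standardised difference between two groups: "Mean difference at 6-month outcome (9.93) and pooled standard deviation (19.77) values were obtained from this study to calculate a standardised mean difference". The design is set "at 0.05 significance, 0.8 power and 20% attrition", giving 160 participants, 80 per arm. No correlation between baseline and 12-month FFI pain is used or reported.

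**The concern.** In a randomised trial, baseline differences between arms arise by chance. Seeing one does not show which covariates belong in the model. What matters is how strongly a covariate predicts the outcome, and the baseline value of the outcome itself is the natural candidate whether or not the arms happen to differ on it.

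The rule leaves three things open:

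- what counts as an imbalance, and on which variables;
- which covariates may enter once one is declared;
- what the primary model is if none is declared.

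Two things are at stake. One is precision: if the trigger does not fire and the fallback is unadjusted, the information in baseline FFI pain is not used. The other is error control: if the choice between models is made after results by arm are visible, the reported p-value and confidence interval need not have their stated properties.

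The open fallback also matters for the form of the outcome. With baseline FFI pain in the model, analysing the 12-month score or the change score gives the same treatment estimate. Without it the two differ, and the article speaks of the 12-month score in one section and of change scores in the other.

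**Working it through.** **Inputs.** From Sample size: mean difference 9.93, SD 19.77, two-sided alpha 0.05, power 0.80, attrition 20%, 80 per arm. Assumed, because the article gives no value: correlation r between baseline and 12-month FFI pain of 0.3, 0.5 or 0.7.

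**Step 1: reproduce the plan's figure.** The standardised difference is d = 9.93/19.77 = 0.502. The normal formula n = 2(1.96 + 0.84)²/d² gives 63 per arm; 63/0.8 rounds up to 79, or 158 in total. The t-test version gives 64 per arm, and 64/0.8 = 80, or 160 in total. The stated size is therefore that of an unadjusted two-sample t-test with 64 completers per arm.

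**Step 2: ANCOVA fitted whatever the balance.** Adjusting for baseline FFI pain multiplies the residual SD by √(1 − r²), so power ≈ Φ(d√(n/2)/√(1 − r²) − 1.96). With n = 64, d√(n/2) = 0.502 × √32 = 2.841.

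- Unadjusted: Φ(2.841 − 1.96) = Φ(0.881) = 0.81
- r = 0.3: Φ(2.841/0.954 − 1.96) = Φ(1.019) = 0.85
- r = 0.5: Φ(2.841/0.866 − 1.96) = Φ(1.321) = 0.91
- r = 0.7: Φ(2.841/0.714 − 1.96) = Φ(2.019) = 0.98

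**Step 3: a conditional rule.** The article does not define its rule, so this one is a stand-in: test baseline FFI pain for a difference between arms, use ANCOVA if p is below a threshold, otherwise use an unadjusted t-test on the 12-month score. The simulation used 40,000 trials per setting with 64 per arm. The trigger fired in about 5% of trials at the 0.05 threshold and about 20% at the 0.20 threshold.

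| r | ANCOVA always, power (simulated) | 5% trigger, power | 20% trigger, power | 5% trigger, type I error | More favourable of two models, type I error |
|---|---|---|---|---|---|
| 0.3 | 0.84 | 0.81 | 0.82 | 0.048 | 0.064 |
| 0.5 | 0.90 | 0.82 | 0.84 | 0.042 | 0.072 |
| 0.7 | 0.98 | 0.82 | 0.86 | 0.034 | 0.08 |

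The mechanical rule is conservative: the unadjusted test is used only when the arms are close at baseline, and its standard error takes no credit for that. The last column is a different situation, in which the analyst may report whichever of the unadjusted and ANCOVA results is more favourable.

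**Step 4: sensitivity to the stand-in.** If k independent baseline variables are each checked at 0.05, the chance that at least one is flagged is 1 − 0.95^k: 23% for k = 5 and 40% for k = 10. A broad check would therefore trigger ANCOVA more often than a single test. If the fallback were an unadjusted change score (SD multiplied by √(2(1 − r))), power would be 0.67, 0.81 and 0.96 at r = 0.3, 0.5 and 0.7, below ANCOVA in each case.

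**The case against.** The strongest reply is that the wording is provisional and the article condensed. It names no significance test, threshold or single variable, and it does not say that the fallback is unadjusted. Since the secondary outcomes are analysed by ANCOVA with baseline values and no trigger, a reader could take baseline-adjusted ANCOVA as the intended family throughout, with the exploration concerning extra confounders only. A final covariate list is commonly left to the SAP. The Discussion also states that the data analysis will be blinded, which limits favourable selection.

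Much of this stands, and it rules out several stronger readings:

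- A reader might infer that the trial is underpowered. It is not: the size was set for an unadjusted comparison and still gives about 0.80.
- A reader might infer that the plan commits to an unadjusted test in about 95% of trials. That needs one 5% test on one variable and an unadjusted fallback, and the article states neither.
- A reader might infer that the rule inflates type I error. Applied mechanically at 5% it does the opposite; inflation needs a choice between results that are already visible.
- A reader might extend the trigger to the secondary outcomes. The text does not repeat it there.

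What does not stand is treating this as silence for the SAP to fill. The article states a condition for the primary analysis, and an SAP that adjusted unconditionally would have to depart from it. Blinding the analyst reduces selective choice but does not define the model or recover the precision.

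**Conclusion.** The point holds as a free improvement. As written, the primary model depends on an undefined finding in the trial data, and baseline FFI pain is not assured a place in it. The planned power is intact; what may be forgone is the gain from 0.81 unadjusted to about 0.85, 0.91 or 0.98.

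The size of that gain rests on the assumed r. At 0.3 it is modest; at 0.5 or above it is substantial. The eligibility floor of 20 mm foot pain may narrow the spread of baseline pain, so the lower values should not be dismissed. How much of the gain would actually be lost rests on the stand-in trigger and on an unadjusted fallback. The type I figures of 0.064 to 0.08 are a worst case under free choice between two models, not a property of the stated rule and not a statement about intent.

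The use of change in DAS-28, which is measured after randomisation, as an example covariate is a separate matter. None of these figures depend on it.

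**What to change.** In the Analysis section, delete the imbalance condition and the data-driven search for confounders. Replace them with a statement such as: the primary analysis is an ANCOVA of 12-month FFI pain on arm and baseline FFI pain, whatever the observed balance, with any further baseline covariates listed here and fixed before between-arm data are seen. Baseline DAS-28 and site are possible candidates, but the point does not depend on adding them.

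The secondary outcomes already have ANCOVA with baseline values. Only their open-ended reference to potential confounders needs the same closed list.

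The cost is wording in the protocol or SAP. Table 1 already schedules FFI pain and DAS-28 at baseline, and the sample size need not change.

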## Methods/design

### Study design and setting

This trial is designed as a multi-centre two-arm parallel RCT. A CONSORT flow diagram is presented (Fig. 1), which outlines the flow of participants through the trial. Participants will be identified by their Rheumatologist within the early RA clinics in National Health Services Grampian, Fife, Lanarkshire, Lothian Health Boards (Scotland), as well as Dorset Healthcare University Trust, and Homerton University Hospital (England). Each site will have an appointed independent outcome assessor (either a rheumatology nurse specialist or a research nurse) who has received trial protocol training, and at least one United Kingdom registered Health Care Professionals Council podiatrist who has either musculoskeletal or rheumatology experience working at least at an National Health Service band 6 level and who has received trial specific intervention delivery training. The intervention will be supplied by the podiatrist and the outcomes will be collected by the outcome assessor at each site over three time points: baseline, and 6 and 12 months from baseline. Recruitment commenced May 2016 and the study end (final follow-up, final participant) is anticipated by 30th April 2019.

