### Secondary outcome measures

The remaining FFI subscales for disability (FFI_dis_) and functional limitation (FFI_fl_) will be measured as secondary outcomes. In addition, the Foot Impact Scale for RA (FIS_RA_) will be adopted as a secondary outcome measure to provide a disease-specific measurement of localised disease impact [54]. This is a 51-item questionnaire with dichotomous scoring system (true/not true responses) and two subscales for impairment/footwear and activity limitation/participation restriction. Responses in the true column are summated to give a total score for each subscale.

The EQ-5D-5 L [55] is a valid and reliable measure of health-related quality of life in adults and will be used primarily for the purposes of the cost-utility analysis aspect of the embedded health economic evaluation of the intervention. The EQ-5D-5 L is a 5-item questionnaire that requires a response on a 5-point Likert scale, and responses will be used to calculate quality-adjusted life years gained.

A satisfaction questionnaire consisting of numerical rating and Likert scales will be used to measure orthotic device comfort, fit, and self-reported efficacy symptoms and activity levels. Participant reporting of adverse events will also be permitted to provide further comments using open-ended responses within this questionnaire. In addition, a small random sample of participants will be invited to take part in an interview to explore experiences of the interventions and perceptions of improved/deteriorated outcomes.

Global disability will be measured using the Health Assessment Questionnaire [56]. Global disease activity will be measured using the Disease Activity Score using 28 joints [57]. Disease duration will be recorded as the time in months from onset of symptoms and time in months from disease diagnosis as self-reported by the participant.

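### The only covariate set spelled out for the primary ANCOVA includes change in DAS-28, a post-randomisation variable; adjusting for it can bias the intention-to-treat effect on foot pain

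*Protocol article*

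**What the plan says.** The protocol article defines the primary endpoint plainly: "The primary outcome measure will be foot pain, which will be measured at 12 months using the Foot Function Index pain subscale". The Analysis section opens with an intention-to-treat commitment and then makes the adjusted model conditional: "Should we detect any imbalances between intervention groups, we expect that the analysis of the primary outcome" will be by ANCOVA, "with adjustment for relevant baseline values and potential confounders". It illustrates this in firmer words: "For example, to account for systemic disease activity as a covariate, the FFI pain subscale change scores will be adjusted" for "both FFI pain subscale baseline scores and the change scores of the Disease Activity Scale for 28 joints between baseline and follow up". No other covariate set is given for the primary outcome.

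On timing, the Study design and setting section says that "outcomes will be collected by the outcome assessor at each site over three time points: baseline, and 6 and 12 months from baseline". Table 1 marks DAS-28 at baseline, 6 months and 12 months, and places allocation after baseline, at the first clinical visit. Under the heading Secondary outcome measures the article states: "Global disease activity will be measured using the Disease Activity Score using 28 joints".

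**The concern.** A confounder of a treatment comparison must be related to how treatment was assigned. Here assignment is random and made after baseline, so nothing that develops between baseline and follow-up can confound it. The change in DAS-28 is such a quantity. If it responds to the allocated device, or to care given once the allocation is known, it lies on a path from treatment to foot pain or shares causes with foot pain. Conditioning on it then removes part of the real effect or creates an apparent one. The estimate is no longer the total effect that intention-to-treat promises.

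The trigger does not protect against this. If the imbalance detected is a difference between arms in DAS-28 change, the adjustment is made in just the situation where it biases. Nor is the change score the right tool for a chance imbalance in disease activity at entry; the baseline value is. What is at stake is the headline estimate of customised versus prefabricated orthoses at 12 months.

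**Working it through.** **1. The plan's own figure.** From the Sample size section: difference 9.93, SD 19.77, two-sided alpha 0.05, power 0.80, attrition 20%. The standardised difference is 9.93/19.77 = 0.502. A two-sample t-test needs 63.2 per arm (63.8 if 0.5 is used), so 64. Then 64/(1 − 0.20) = 80 per arm, 160 in total. The stated figure reproduces, and it does not depend on any covariate.

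**2. Is DAS-28 change pre- or post-randomisation?** Table 1 puts allocation after the baseline measurement and follow-up DAS-28 at 6 and 12 months. The change score therefore contains a post-allocation measurement.

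**3. Direction and size of the bias.** The model is linear, with baseline FFI pain in it. Once baseline FFI pain is a covariate, analysing the change score or the 12-month score gives the same treatment coefficient, so the change-score outcome is not the issue. Let:
- τ = 9.93, the true total benefit (Sample size section);
- n = 64 completers per arm (80 × 0.8);
- ρ = 0.5, the correlation of baseline with 12-month FFI pain (**assumed**);
- g = difference between arms in DAS-28 change, in SD units, with DAS-28 lower in the arm with less pain (**assumed**);
- r = within-arm correlation of DAS-28 change with FFI pain left over after baseline adjustment (**assumed**).

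Residual SD = 19.77 × √(1 − 0.5²) = 17.12.

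Adjusted estimate = τ − r × 17.12 × g.

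SE = 17.12 × √(1 − r²) × √(2/64) × √(1 + g²/4).

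Power and type I error use the t distribution with 124 degrees of freedom (128 − 4 parameters). Type I error is computed with τ = 0.

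| g | r | Bias | Estimate | Power | Type I error |
|---|---|---|---|---|---|
| no DAS-28 covariate | – | 0 | 9.93 | 0.90 | 0.05 |
| 0 | 0.3 | 0 | 9.93 | 0.93 | 0.05 |
| 0 | 0.5 | 0 | 9.93 | 0.96 | 0.05 |
| 0.1 | 0.3 | 0.51 | 9.42 | 0.90 | 0.05 |
| 0.1 | 0.5 | 0.86 | 9.07 | 0.93 | 0.06 |
| 0.2 | 0.3 | 1.03 | 8.90 | 0.86 | 0.06 |
| 0.2 | 0.5 | 1.71 | 8.22 | 0.87 | 0.10 |
| 0.3 | 0.3 | 1.54 | 8.39 | 0.81 | 0.08 |
| 0.3 | 0.5 | 2.57 | 7.36 | 0.79 | 0.16 |

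Example, last row: 0.5 × 17.12 × 0.3 = 2.57, and 9.93 − 2.57 = 7.36. Starting from exactly 0.5 SD (9.885) gives 7.3.

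If the shift goes the other way, the sign reverses and the estimate is inflated by the same amount (12.50 in the last row). If r = 0, the bias is zero whatever g is.

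**The case against.** The strongest reply is that the adjustment is not a fixed rule. The text says that data will be explored, that ANCOVA is expected if imbalances are seen, and that DAS-28 change is an example. This stands. A reader might infer that the primary model is settled and will include DAS-28 change; the wording does not go that far. But the example says the scores will be adjusted, and no alternative model is offered.

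A second reply is that both arms receive active orthoses and DAS-28 is a global score, so the shift between arms may be close to nil. This also stands. A 0.2 to 0.3 SD shift would be 40 to 60% of the 0.5 SD assumed for foot pain itself, and the protocol gives no basis for it. With no shift, DAS-28 change acts as a prognostic covariate and power rises from 0.90 to between 0.93 and 0.96 under the assumptions above. A reader might take the Health economic evaluation section, where "the costs of systemic therapies in terms of biological agents, disease-modifying anti-rheumatic drugs and non-steroidal anti-inflammatories will be recorded for both trial arms", as a sign that drug use will differ by arm. It shows only that costs are collected in both. With unblinded participants and treating clinicians a difference is possible, no more.

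Third, whether DAS-28 is a secondary outcome is arguable. It stands under that heading, but neither the abstract nor secondary aim (i) names it. The argument needs only its timing.

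Finally, a reader might infer that participants with 12-month FFI pain but no 12-month DAS-28 would be excluded. The Missing data section leaves imputation open, Table 1 schedules both measures at the same visits, and complete-case analysis is stated nowhere. That inference is not supported.

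**Conclusion.** Wrong as written, and it should be fixed. The article offers a post-randomisation change score as its example of a variable to adjust for in a randomised comparison, and conditioning on it can move the primary estimate away from the intention-to-treat effect. Bias requires both a shift in DAS-28 change between arms and a correlation of that change with foot pain. A reader might infer that any such adjustment is biased; it is not if either condition fails.

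Under shifts of 0.1 to 0.3 SD and correlations of 0.3 to 0.5, the loss is about 0.5 to 2.6 of 9.93 points, or 5 to 26%. Type I error runs from barely above 0.05 to 0.16, the top value needing the most extreme combination. These figures rest on assumed g, r and ρ, a linear model, 64 completers per arm, and DAS-28 change unrelated to baseline pain. The true bias could be negligible. The reason to act is that the protocol leaves the headline estimate open to an untested assumption when a safe covariate is already to hand.

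**What to change.** In the Analysis section, replace the change in DAS-28 with baseline DAS-28. State the primary model in advance as 12-month FFI pain on arm, baseline FFI pain and baseline DAS-28, applied whatever imbalance is observed. Replacing the covariate alone is not enough: if the trigger stays, the model would still be chosen after looking at the data. Keep DAS-28 change as an outcome, or use it in an analysis labelled exploratory (mediation) and reported apart from the primary result.

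The cost is a sentence or two of text. Baseline DAS-28 is already scheduled in Table 1, and the sample size of 160 is unaffected. The downside is losing the precision that DAS-28 change would bring if it were truly unaffected by arm, about 0.03 to 0.06 of power under the assumptions above. Baseline FFI pain alone already gives power of about 0.90 at an assumed baseline correlation of 0.5.
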